# Support for young people who are distressed by hearing voices: protocol for an uncontrolled feasibility evaluation of a psychological intervention package delivered within secondary schools (the ECHOES study)

**DOI:** 10.1186/s40814-025-01611-x

**Published:** 2025-04-04

**Keywords:** Voice hearing, Young people, Coping, Schools, Feasibility

## Abstract

**Background:**

Hearing voices is a common experience for young people and can cause significant distress. There are no evidence-based psychological interventions for distressing voices in young people, although a focus on coping strategies has been suggested as a useful approach. We have developed and evaluated a brief 1:1 coping intervention for young people who hear distressing voices. This intervention has been successfully piloted within Child and Adolescent Mental Health Services (CAMHS), together with a psychoeducational workshop for parents. The 1:1 intervention and the workshop will be combined into an intervention package and offered within schools to maximise accessibility.

**Methods:**

This study will be an uncontrolled feasibility evaluation addressing the following questions: is the intervention package acceptable to young people, those who support them, and staff and practitioners within secondary schools? What is the optimum content, structure, and duration for the intervention package? Is delivery of the intervention package feasible for the practitioners and what are their requirements for training and supervision? What tools can be used to evaluate the impact of the intervention package?

The study will be guided by the MRC Framework for the development of complex interventions and consist of an iterative process over four phases: phase 1—adaptation of the intervention package with young people, parents, and school staff; phase 2—delivery of the intervention package through Mental Health Support Teams to students, supporters who have been nominated by the students and school staff; phase 3—analysis of quantitative and qualitative data collected from participants and practitioners; phase 4—further adaptation of the intervention package with young people, parents and school staff.

**Discussion:**

If the findings from the study suggest that a future trial is warranted, a feasibility Randomised Controlled Trial will be designed to establish the parameters for a definitive trial.

**Trial registration:**

Current Controlled Trials ISRCTN registration number: 16395888. Registered on 11 January 2024. 10.1186/ISRCTN16395888.

**Supplementary Information:**

The online version contains supplementary material available at 10.1186/s40814-025-01611-x.

## Background

The experience of hearing voices (also known as auditory hallucinations) is a common experience for young people, with prevalence rates estimated at 12% [1]. This experience has been associated with an increased risk for suicidal ideation, plans and attempts [2], and self-harm [3]. When voice hearing persists in young people, this can be indicative of severe mental health problems in the future [4], including psychosis [5]. Young people have reported feeling lost, not listened to, and found it difficult to obtain useful information when seeking help for voice hearing within mental health services [6]. They also report many barriers to disclosure [7]. The individuals from whom young people may seek help have also reported a lack of confidence to talk about voice-hearing and offering advice (e.g. mental health practitioners [8], parents [9], and teachers [10]).

There are currently no psychological interventions that have an evidence base specifically for the treatment of distressing voices for young people. A focus on coping strategies has been suggested by young people as a useful approach to intervention [11]. Within the Sussex Voices Clinic (https://www.sussexpartnership.nhs.uk/sussex-voices-clinic) we have developed a brief coping intervention for the treatment of distressing voices in young people. This intervention was piloted within CAMHS [12] and generated pre-post reductions in voice-related distress. Feedback from young people was suggestive of the value of a space to talk about voices (e.g. ‘[the therapist] was easy to talk to and just listened without judging’) and a focus on coping strategies (e.g. ‘it taught me lots of different ways to block out the voice, move forward and not dwell on things’) [12]. We also piloted a psychoeducational online workshop that was offered to parents/carers and outcomes suggested that participants were more confident to offer useful advice about voice-hearing to a young person [13].

We will combine the brief coping intervention and the psychoeducational workshops to form an intervention package to be delivered within schools where early intervention and accessibility can be maximised. This will be facilitated by the Mental Health Support Teams in Schools (MHST) initiative, a national initiative whereby trained mental health practitioners are located within schools to address the psychological wellbeing of young people [14].

The study will address the feasibility of offering an intervention package within secondary schools to young people who hear distressing voices and the people who support them.

## Methods

### Aim and research questions

The study will be an uncontrolled feasibility evaluation guided by the MRC Framework for the development of complex interventions [15] and consist of an iterative process that will proceed over four phases: phase 1—development of the intervention package; phase 2—delivery of the intervention package; phase 3—collection and analysis of quantitative and qualitative data; and phase 4—co-evaluation of the intervention package.

The following questions will be explored as the intervention package is ‘tested and refined on a small scale’ [16]

Is the intervention package acceptable to young people, those who support them, and staff and practitioners within secondary schools?What is the optimum content, structure, and duration of the intervention package?Is delivery of the intervention package feasible for the MHST practitioners and what are their requirements for training and supervision?What tools can be used to evaluate the impact of the intervention package?Can participants be retained within the study and offer full datasets?

### Setting

The study will be conducted within the secondary schools that are part of the Mental Health Support Teams (MHST) in Schools initiative in West Sussex—called Thought-Full. This initiative is co-ordinated jointly by Sussex Partnership NHS Foundation Trust and West Sussex County Council. There are currently 13 secondary schools that have become established within Thought-Full (others are in set-up), each of which receives support from Education Mental Health Practitioners (EMHP) and Senior Mental Health Practitioners (SMHP) to deliver evidence-based low-intensity psychological interventions, develop the whole school approach to mental health and well-being and help students to get the right support.

### Inclusion and exclusion criteria

Volunteers (phases 1 and 4—we refer to these participants as ‘volunteers’ to differentiate them from the ‘participants’ who will take part in phases 2 and 3):

Students will be students within years 7–11 (ages ranging from 11 to 16 years) at one of the schools served by Thought-Full. There will be no criterion related to personal experience of hearing voices and/or mental health problems. The students will need to be willing and able to provide written informed assent. Assent to approach the student’s parent/carer will be required for all students. The parent/carer of the students will need to give written informed consent.Parents will be parents of students within years 7–11 at one of the schools served by Thought-Full. There will be no criterion related to the student or the parent having personal experience of hearing voices and/or mental health problems. It will be permitted (but not required) for the parent’s child to be a volunteer within the student’s group.School staff will be permanent members of staff at one of the schools served by Thought-Full. There will be no criterion related to the staff having pastoral responsibilities within the school.

Participants (students—phases 2 and 3):

Attending one of the schools selected for participation in phase 2Within years 7–11 of the selected schoolsWilling and able to provide written, informed assent. Assent to approach the student’s parent/carer will be required for all students. The parent/carer of the student will need to give written informed consent.Reporting a current voice-hearing experience—operationalised by participants having a score of at least 1 on item 1 on the Hamilton Voices Questionnaire (HPSVQ) [17]—indicating that the participant has experienced at least one episode of voice-hearing in the past weekReporting that voice-hearing experiences are causing distress—operationalised by a score of at least 8 (range from 0 to 16) on the negative impact scale of the HPSVQNot a volunteer in this study

Participants (Plus-1s [a trusted adult selected by the student]—phases 2 and 3):

Nominated by one of the student participantsAged 16 years or overWilling and able to provide written informed consent.Not a volunteer in this studyNot a student in secondary education.

Participants (school staff—phases 2 and 3).

A member of permanent staff at one of the selected schoolsWilling and able to provide written informed consentNot a volunteer in this study

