### Clinical outcome measures

The process of selecting outcome measures for use in phase 2 will be guided by the consultations with volunteers in phase 1. We will offer the volunteers a range of candidate measures to inform their discussions, e.g. the Hamilton Voices Questionnaire [17] (used within our evaluation of the coping intervention within CAMHS) [12]; the Manchester Voices Inventory for Children [19] (developed by [name] to assess the voice-hearing experiences of young people), the Strengths and Difficulties Questionnaire (routinely used within the MHST) [20], the Revised Child Anxiety and Depression Scale (routinely used within the MHST) [21] and the Attitudes and Beliefs Towards Voice Hearing measure (used within our evaluation of the psychoeducational workshops) [13].

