0	Potential volunteer receives PIS from an approved source	
1	Contact is made with potential volunteers to set up the eligibility and consent meeting	Researcher
1	Volunteer can ask questions, complete the eligibility assessment, and complete the consent form	Researcher
2	Contact will be made to arrange the stakeholder meetings	Researcher
3–12	Phase 1 stakeholder meetings will be conducted	Researcher
13–56	Occasional email/text/phone contact to maintain engagement	Researcher
57–69	Phase 4 stakeholder meetings	Researcher

^a^Relates to the duration of the volunteer’s time in the study, not to the study timeline

#### Phase 2

Participants will be recruited from a sub-set of selected secondary schools within Thought-Full. Decisions about the schools to be selected will be guided by the capacity of schools (e.g. availability of Thought-Full practitioners) and the needs of the local population (e.g. indices of deprivation, SEN data, ethnicity data, and referrals to established emotional well-being community services and CAMHS). Students will be referred through the usual Thought-Full processes via self-referral or via parent/school staff; Plus-1s will be nominated by referred students and the student will provide the Plus-1 with a PIS and ask them to contact the research team if they wish to participate; and school staff will self-refer. The opportunity to participate will be advertised through the usual promotional channels used by Thought-full. Approximately 32 participants will be recruited for each of the three groups: students, Plus-1s, and school staff. All those who express an interest in participating will be sent a PIS and have at least 48 h to review its contents. Each prospective participant will be invited to a meeting with the RA where informed assent/consent will be given, eligibility will be confirmed, and baseline measures completed. Thereafter, each participant will be offered the appropriate element of the intervention package; the 1:1 coping intervention for students; the psychoeducation workshop for the Plus-1s; and a separate psychoeducation workshop for school staff. See Table 2 for the participant’s journey through the study.

**Table 2 Tab2:** Participant journey (phases 2 and 3)

Week^a^	Event	Who
0	Advertise research participation opportunity through approved channels and processes	Researcher
0	Potential participant receives PIS from approved source	

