0	Referral made where the potential participant is interested in participation	MHST or Teaching staff
1	Contact is made with potential participant to set up the eligibility and consent meeting	Researcher
1	Participant can ask questions, complete the eligibility assessment, complete the consent form and the baseline assessment	Researcher
2	Contact will be made to arrange the intervention session(s)	Researcher or MHST staff
3–12	Intervention session(s) will be delivered	MHST staff
13–14	Final assessment meetings	Researcher

^a^Relates to the duration of the participant’s time in the study, not to the study timeline

#### Phase 3

After the completion of the intervention, participants will be invited to a final assessment meeting where measures will be completed, and feedback will be sought. The meetings will be facilitated by [name] and the RA and will be offered on a 1:1 basis for student participants and as separate focus groups for Plus-1 participants and school staff participants. The meetings will take place either in person or remotely, depending on the location, availability, and preferences of the participants. The EMHPs and SMHPs who deliver the intervention package will be invited to a separate focus group to reflect upon their experience and will be asked to provide an anonymously written reflection, which will ensure we account for biases inherent in face-to-face qualitative work where the designers of the intervention also evaluate the process. The student participants and Plus-1 participants will be reimbursed with a £20 voucher after attending each of the assessment meetings (baseline assessment and final assessment). The school staff participants will not be reimbursed as they will be attending assessment meetings in paid time.

#### Phase 4

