### Data analysis

Qualitative—phase 1: a consensus amongst the groups as to the most important content and communication style for the intervention package within a school setting will be achieved through the process of concept mapping [26]. In their groups, the volunteers will identify important features of the intervention [27]. Through a process of facilitated negotiation and conversation, the groups will develop consensus maps (construct maps, akin to mind maps in presentation) of the key features they think should be included in the intervention package.

Quantitative—phases 2 and 3: recruitment and retention rates will be calculated for the data generated and used to assess the feasibility of delivering the intervention package and its acceptability. The level of study diversity and inclusion will be assessed through a summary of the demographics using descriptive statistics as appropriate. Quantitative measures included in the evaluation tools will also be summarised using descriptive statistics. Quantitative measurements collected pre- and post-intervention will be used to indicate average levels of change with associated 95% Confidence Intervals, but no hypothesis testing will be carried out. This information will be for indicative purposes only. Levels of data completeness will be summarised.

Qualitative—phase 3: the final assessments are expected to last between 40 and 90 min, depending on how much people would like to say. Discussions about feedback will be informed by a Topic Guide and will follow a flexible structure to enable the participants to lead the conversation. Questions and prompts will be asked by the researcher to encourage reflection on experience and elicit information to inform the ongoing development of the intervention materials.

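### If the HPSVQ is kept as a student outcome and its eligibility score serves as baseline, regression to the mean will shift the reported pre-post change towards improvement

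*Protocol article*

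**What the plan says.** Under Inclusion and exclusion criteria, a student participant must report a current voice-hearing experience and distress. Distress is "operationalised by a score of at least 8 (range from 0 to 16) on the negative impact scale" of the HPSVQ.

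Under Recruitment, Phase 2, each prospective participant has one meeting with a research assistant at which "informed assent/consent will be given, eligibility will be confirmed, and baseline measures completed". Table 2 repeats this as a single week-1 event ("complete the eligibility assessment, complete the consent form and the baseline assessment"). Intervention sessions run in weeks 3 to 12, and the next listed measurement is "Final assessment meetings" in weeks 13 to 14. No second reading before the intervention is listed.

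The Clinical outcome measures section leaves the outcomes open: "We will offer the volunteers a range of candidate measures to inform their discussions, e.g. the Hamilton Voices Questionnaire". The choice is guided by the phase 1 consultations. Table 3 (amendment 3) adds a Goal Based Outcomes measure for students in phase 2.

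Under Data analysis, "Quantitative measurements collected pre- and post-intervention will be used to indicate average levels of change with associated 95% Confidence Intervals". There is no hypothesis testing, and the result is described as indicative. There is no control group.

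**The concern.** A student's score in any one week is a stable level plus a temporary fluctuation. A cut-off at 8 selectively admits students whose fluctuation happened to be upward that week. When they are measured again, the fluctuation is on average zero and the mean falls, whether or not the intervention did anything. If the admitting score is also the pre value, the whole of that fall enters the estimated change. The confidence interval describes sampling error around this shifted centre, so it does not warn the reader. A control arm would normally absorb the artefact, and here there is none.

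At stake is the credibility of a published estimate of student change. It would look like a signal of benefit and could colour informal thinking about the feasibility randomised trial mentioned in the Discussion.

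**Working it through.** **The plan's own figure.** The Sample size section inflates 24 interviews per group for 25% attrition: 24 / (1 − 0.25) = 32. This reproduces. The same attrition leaves 32 × 0.75 = 24 students with pre and post values.

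**Inputs from the protocol.** Entry cut-off of at least 8 on a 0 to 16 scale; one meeting for eligibility and baseline; mean change with a 95% interval; 32 students recruited, about 24 completing.

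**Inputs that are assumptions.** The protocol gives no HPSVQ mean, SD or test-retest correlation. The ranges used for referred students are mean μ = 6 to 12, SD σ = 3 to 4 and correlation r = 0.5 to 0.9, with no true change.

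**Formula.** Scores are integers, so the cut lies at 7.5. With a = (7.5 − μ)/σ, the expected fall under no change is (1 − r) × σ × φ(a) / [1 − Φ(a)].

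- Central case, μ = 8, σ = 4, r = 0.7: a = −0.125, φ(a) = 0.396, 1 − Φ(a) = 0.550, ratio 0.720. Fall = 0.3 × 4 × 0.720 = 0.86.
- High end, μ = 6, σ = 4, r = 0.5: a = 0.375, ratio 1.051. Fall = 0.5 × 4 × 1.051 = 2.10.
- Low end, μ = 12, σ = 3, r = 0.9: a = −1.5, ratio 0.139. Fall = 0.1 × 3 × 0.139 = 0.04.

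**Simulation check.** Scores were generated as true level plus error, rounded, limited to 0–16, selected at 8 or more, and re-measured with no change. The last column is the share of 24-pair t intervals lying wholly on the improvement side (nominal 2.5%).

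| Mean | SD | r | Share of referred students eligible | Mean fall | SD of change | Intervals wholly on improvement side |
|---|---|---|---|---|---|---|
| 6 | 4 | 0.5 | 35% | 2.11 | 3.56 | 80% |
| 6 | 4 | 0.7 | 35% | 1.27 | 2.90 | 54% |
| 8 | 4 | 0.7 | 55% | 0.87 | 2.87 | 30% |
| 10 | 4 | 0.7 | 73% | 0.55 | 2.80 | 15% |
| 12 | 4 | 0.7 | 87% | 0.30 | 2.64 | 7% |
| 12 | 3 | 0.9 | 93% | 0.04 | 1.31 | 4% |

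For scale, the central-case interval half-width with 24 pairs is 2.069 × 2.87 / √24 = 1.21 points, so a shift of 0.87 is about 70% of it (0.87 / 1.21 = 0.72).

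**Other measures taken at the same meeting.** They were not used for selection. They share the cut-off effect only as far as their own week-1 fluctuation correlates with that of the HPSVQ: not at all if the two are unrelated, in part otherwise. The protocol offers nothing from which to size this.

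**A separate baseline.** When change was simulated from a second reading on which nobody was selected, the mean bias was about 0.00 and 2.3% to 2.6% of intervals lay wholly on the improvement side. This assumes that the fluctuation at screening has passed by the second reading.

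**The case against.** The strongest reply is that the protocol never says the bias must occur. The HPSVQ is one example in a list, the volunteers guide the choice, and no sentence states that the eligibility score is reused as the pre value. That stands, and it is why the point is conditional. A reader might infer from the shared meeting that the artefact is certain; the text does not go that far. It does schedule no other reading before the intervention, so if the HPSVQ is chosen, the week-1 score is the only pre value on offer.

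Second, a reader might infer that the decision to proceed is compromised. It is not. The Progression criteria rest on recruitment, full datasets and participant feedback, and change is not among them. Nor would HPSVQ change be the only quantitative signal for students, since the Goal Based Outcomes measure has been added.

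Third, the plan calls the change indicative and rules out testing. This properly limits what may be concluded, but it does not move the interval back to the right centre.

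Fourth, the size depends on assumed inputs. That also stands. If most referred students score well above 8, the effect is negligible. The larger values need a referred population of which roughly a third passes the cut-off.

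The point cannot simply be left to an analysis plan, because a later document cannot recover a reading that the visit schedule did not collect.

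**Conclusion.** The point holds in conditional form. If the HPSVQ is retained as a student outcome and the admitting score is its baseline, the mean change and its 95% interval will be biased towards improvement. The direction is certain under those two conditions. The size is not: about 0.04 to 2.1 points on the 0 to 16 scale over the assumed ranges, with 0.87 points in the central case, where about 30% of 24-pair intervals would suggest improvement when there is none. Plus-1s and school staff are not selected on a score and are unaffected. The sample size and the progression rule are untouched. This should be corrected because it bears on a reported estimate and costs little, but it does not threaten the feasibility aims.

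**What to change.** If the HPSVQ is chosen as a student outcome, have students complete it again just before session 1 and report change from that reading to the final assessment. Show the change from screening to session 1 beside it, labelled as pre-intervention change. It should not be called untreated, because the Intervention protocol allows other interventions throughout.

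If a repeat is not feasible, name a measure not used for entry, such as the Goal Based Outcomes measure, as the main student pre-post measure. Report any HPSVQ change together with the regression to the mean expected from the formula above. The mean and SD can come from the scores of all students screened, with r over a stated range. This alternative reduces the problem but may not remove it, for the reason given about correlated fluctuation.

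The volunteers' choice of outcomes is left as it is; the repeat is needed only if they keep the HPSVQ.

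The cost is a few minutes of questionnaire time per student, one more form, and a sentence in the analysis text. Research assistants collect the measures while practitioners deliver session 1, so someone must be assigned to administer the form. The extra form should not count towards the full-dataset criterion, so that it does not make the 75% target harder to reach.
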